### **3.7 Study Outcomes**

1. Primary outcome: Pregnancy continues until 34w0d of gestation or documentation of lung maturity at 32w0d to 33w6d.

2. Secondary outcomes:

a. duration of latency period (time from randomization to delivery)

b. composite neonatal morbidity, defined as one or more of the following, using the definitions of Mercer et al. (1997):

i. stillbirth

ii. neonatal death

iii. infant death before hospital discharge

iv. respiratory distress syndrome (RDS)

v. intracranial hemorrhage (ICH), grade 3 or 4

vi. necrotizing enterocolitis (NEC), stage 2 or 3

vii. documented neonatal sepsis within 72 hr of birth

viii. periventricular leukomalacia (PVL): characteristic lesions in the subcortical white matter seen on cerebral imaging studies within 96 hrs of birth (not included in the definitions of Mercer et al. (1997))

3. Tertiary outcomes

a. gestational age at delivery

b. route of delivery

c. neonatal length of stay

d. birth weight

e. Apgar scores

f. Amnionitis

g. Postpartum endometritis

### **3.8 Data Collection**

A Case Report Form (CRF) will be used to capture all primary, secondary, and tertiary data. The original CRF will remain in a locked file at the study site and a copy will be faxed to the central data center for computer entry. The CRF will reflect events until the mother & newborn are both discharged from the hospital. If the infant remains hospitalized at 60 days after birth, the CRF will reflect all events in the first 60 days of life.

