#### **3.2 Inclusion Criteria, Outline**

Definitions of terms and details regarding these criteria are elaborated in the next section, starting on page 13.

1. Participant is 18 years old or older
2. Gestational age is between 23w0d and 31w6d, inclusive, at time of enrollment
3. Singleton pregnancy
4. PROM defined as either (a) or (b) or (c) below
  - (a) Documentation of vaginal leakage of indigo carmine dye instilled via amniocentesis
  - (b) Positive Amnisure® test
  - (c) Two or more of (i) through (iv):
    - i. Nitrazine test with pH of 7 or more
    - ii. Positive fern test
    - iii. Gross pooling of clear fluid in vaginal posterior fornix
    - iv. Ultrasound exam showing oligohydramnios
5. No contraindication to expectant management, including

- a. Suspected intraamniotic infection
  - b. Active preterm labor
  - c. Nonreassuring fetal heart rate tracing
  - d. Intrauterine fetal death
  - e. Preeclampsia
  - f. Active bleeding from uterus
  - g. Fetal lung maturity documented on amniotic fluid specimen prior to enrollment
6. No fetal condition likely to cause serious neonatal morbidity independent of gestational age, including:
- a. Malformation likely to require surgery
  - b. Malformation involving vital organs
  - c. Fetal viral infection
  - d. Hydrops fetalis
7. No history of allergy to 17P or the oil vehicle
8. No medical condition that might adversely interact with 17P
- a. asthma requiring medications
  - b. renal insufficiency (serum creatinine 1.2 mg/dl or more)
  - c. seizure disorder
  - d. ischemic heart disease
  - e. active cholecystitis
  - f. impaired liver function
  - g. history of venous thromboembolism
  - h. history of breast cancer

- i. history of depression requiring hospitalization
- 9. No medical condition treated with systemic steroid medications
- 10. No cervical cerclage present at the time of PROM
- 11. Informed consent obtained & signed

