### **3.9 Data Analysis**

Primary Outcome. The primary outcome measure is the proportion of women who continue the pregnancy to a favorable gestational age (34w0d or documented fetal lung maturity at 32w0d to 33w6d). The null and alternative hypotheses are as follows:

$$H_0: p_1 = p_2 \text{ and } H_1: p_1 \neq p_2$$

where  $p_1$ =the proportion of women who continue the pregnancy to a favorable gestational age in the progesterone group and  $p_2$ =the proportion of women who continue the pregnancy to a favorable gestational age in the placebo group

To test the null hypothesis, a Cochran-Mantel-Haenszel test will be used, stratified by gestational age group at randomization. The final alpha level will be based on the O'Brien-Fleming spending function and depends on the number and timing of interim analyses. If, as planned, only one interim analysis occurs at 50% of participants randomized, the final alpha level will be

0.049. The primary outcome measure will be analyzed in the intent-to-treat population (i.e. all randomized participants).

Secondary Outcomes. The duration of latency will be determined as the time from randomization until delivery. A staggered entry Kaplan-Meier analysis (which adjusts for gestational age at randomization) will be completed with participants with missing outcome data censored on the date last known pregnant. Significant differences between the progesterone and placebo group will be determined using the log-rank test.

The percentage of participants with at least one of the neonatal morbidity measures (composite neonatal morbidity) will be tested for significant differences between the treatment groups using a Cochran-Mantel-Haenszel test stratified by gestational group at randomization. The percentage of participants with each of the component morbidities (e.g. RDS, NEC, IVH, etc.) will be similarly compared.

All secondary outcome measures will be tested for statistical significance using an alpha level of 0.05. Latency and composite neonatal morbidity will be analyzed in the intent-to-treat population. With the exception of stillbirth (analyzed in the intent-to-treat population), the component morbidities will be analyzed in all participants with a live birth.

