### **3.11 Ethical, Legal and Administrative Aspects**

a. Data Quality Assurance. Obstetrix research staff or their designee will conduct a site visit to verify the qualifications of each investigator, inspect the site facilities, and inform the investigator of responsibilities and the procedures for ensuring adequate and correct documentation.

Each investigator is required to prepare and maintain adequate and accurate case histories designed to record all observations and other data pertinent to the study for each study participant. All information recorded on the CRFs for this study, or on correction sheets (query forms or data clarification forms – DCFs) must be consistent with the participants' source documentation (i.e., medical records).

b. Case Report Forms and Source Documentation. All data obtained during this study should be entered on the study specific CRFs accurately and in a timely manner. All source documents from which CRF entries are derived should be present in the participant's medical records. During a monitoring visit, the original CRFs for each participant will be checked against source documents at the study site by the clinical site monitor.

Each CRF and DCF will consist of an original plus a copy. The copy will be forward to a designated person within the Obstetrix Research Team within 30 days of delivery and discharge of both mother and infant. The original will be kept at the site. Instances of

missing or un-interpretable data will be discussed with the investigator and study staff for resolution.

c. Access to Source Data and Monitoring. During the course of the study, a representative of Obstetrix Research team, or a designated representative [a Clinical Research Associate (CRA) or monitor] will make site visits as frequently as necessary to review protocol compliance, compare CRFs and individual participant's medical records, and ensure that the study is being conducted according to pertinent regulatory requirements. CRF entries will be verified with source documentation. The review of medical records will be performed in a manner to ensure that participant confidentiality is maintained.

It is the principal investigator's (PIs) obligation to ensure that documentation of all relevant data such as relevant medical history, date of study enrollment, visit dates, results of examinations or tests, and adverse events is correctly entered in the participant's file.

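### Case report form data end at day 60 for infants still in hospital, but two outcomes are defined by hospital discharge: a death component and neonatal length of stay

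*Protocol*

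**What the plan says.** Section 3.8 makes the case report form (CRF) the source for every outcome: "A Case Report Form (CRF) will be used to capture all primary, secondary, and tertiary data". Its general rule follows infants to discharge: "The CRF will reflect events until the mother & newborn are both discharged from the hospital". It then makes an exception for long stays: "If the infant remains hospitalized at 60 days after birth, the CRF will reflect all events in the first 60 days of life". The protocol describes no later contact and no other data source.

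Section 3.7 includes "infant death before hospital discharge" in the composite neonatal morbidity outcome, separately from neonatal death, and "neonatal length of stay" among the tertiary outcomes. Both run to discharge, and neither carries a 60-day limit.

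Section 3.9 analyses the composite and adds: "The percentage of participants with each of the component morbidities (e.g. RDS, NEC, IVH, etc.) will be similarly compared". It treats stillbirth as one of those components, so the death items belong to the separate comparisons too. It names no method for length of stay.

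Section 3.11 b has the CRF copy sent "within 30 days of delivery and discharge of both mother and infant" and does not mention the 60-day rule.

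**The concern.** The death component and length of stay need information up to discharge, and for some infants the form stops before then. Neonatal death is already its own component and, as usually understood, falls within 60 days. The death-before-discharge item therefore adds only later in-hospital deaths, and those after day 60 are lost. For length of stay, an infant still in hospital at day 60 has no recorded discharge date.

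Whether this happens depends on gestational age at birth, which the trial hypothesises 17P will raise. The extent of truncation can therefore differ between arms and can hide part of a real difference in stay. A statistical analysis plan can choose a censoring method, but it cannot recover dates and deaths that the form never recorded.

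**Working it through.** The plan gives no figure for this point. Its nearest calculation is power for the composite, 60% versus 40% with 111 per group. It reproduces at 81.7% with and 85.1% without continuity correction (the plan says approximately 80%) and does not bear on the gap.

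**Inputs.**
- Cut-off: 60 days = 8w4d (section 3.8).
- Entry: 23w0d to 31w6d (section 3.2), in three 3-week strata (section 3.5).
- Latency half-life: about one week (section 2.2).
- Assumed, because the protocol gives neither: discharge at 36 weeks postmenstrual age (range 35 to 37), and entry either uniform or split 20/30/50 from the lowest to the highest stratum.

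**Age reached at day 60.** Birth age + 8w4d:
- 23w0d gives 31w4d
- 25w6d gives 34w3d
- 28w0d gives 36w4d

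**Birth age below which day 60 comes before discharge.** Discharge age − 8w4d:
- 35 weeks: 26w3d
- 36 weeks: 27w3d
- 37 weeks: 28w3d

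**Share of births before that age.** For entry at day e and cut-off c, the share is 1 − 0.5^((c − e)/7), or zero if e ≥ c. For discharge at 36 weeks, c = 27×7 + 3 = 192 days, and 7/ln 2 = 10.10. Averaging over entry within each stratum:
- 23w0d-25w6d (e from 161 to 182): 1 − (10.10/21) × (0.5^(10/7) − 0.5^(31/7)) = 1 − 0.481 × (0.371 − 0.046) = 0.84
- 26w0d-28w6d (e from 182 to 192 contributes): [10 − 10.10 × (1 − 0.371)]/21 = 0.17
- 29w0d-31w6d: 0

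Uniform entry gives (0.84 + 0.17 + 0)/3 = 0.34. The 20/30/50 split gives 0.2 × 0.84 + 0.3 × 0.17 = 0.22.

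| Discharge (assumed) | Uniform entry | 20/30/50 entry |
|---|---|---|
| 35 weeks | 24% | 14% |
| 36 weeks | 34% | 22% |
| 37 weeks | 45% | 31% |

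With a two-week half-life and discharge at 36 weeks, the figures fall to about 24% (uniform) and 15% (20/30/50).

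These are shares of births before an assumed age. Stillbirths and deaths before day 60 have not been removed, so the share actually in hospital at day 60 is lower, most of all in the lowest stratum.

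**Effect on length of stay between arms.** This is an illustrative simulation with delivery by 34w0d (section 3.6), an assumed discharge SD of 7 days, and an assumed benefit that lengthens the half-life from 7 to 14 days. With uniform entry and discharge at 36 weeks:
- The mean difference falls from 7.3 to 5.8 days when stays are capped at 60, a loss of 1 − 5.8/7.3 ≈ 20%.
- The medians (49.6 and 41.1 days) are the same capped or not.
- Rank-test power at 111 per arm moves from 70% to 69%.

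Across discharge at 35 to 37 weeks, a treated half-life of 10 or 14 days and both entry mixes, the mean difference shrinks by about 8-33%, the medians do not change and power falls by at most about 2 points.

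**The case against.** The strongest reply is that the cut-off is explicit, prespecified and the same in both blinded arms. It truncates both arms alike if the drug has no effect, so type I error is not inflated. Length of stay is tertiary, and its method may properly be left to a statistical analysis plan. A median or rank analysis would hardly notice a cap that fewer than half the infants reach. The composite counts an infant with any one component, and an infant who dies in hospital after day 60 would very probably already count through respiratory distress or another item (an assumption). All of this stands, and it limits the point.

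It does not remove the point. The separately compared death component does not cover the period it names, and no analysis plan can supply the missing discharge dates and deaths.

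A reader might infer more than the protocol supports:
- **That a real two-week benefit disappears.** On the 36-week assumption, births at 25w0d and 27w0d have stays of about 77 and 63 days, and both are recorded as 60. That compares two infants who both lie below 27w3d. Between arms the mean difference is attenuated, not erased.
- **That 84% of the lowest stratum are in hospital at day 60.** That figure is births before an assumed age and ignores stillbirths and early deaths.
- **That sections 3.8 and 3.11 b contradict each other.** One fixes which events the form covers and the other when the copy is sent, so both can be followed. What is missing is the due date for an infant still in hospital at day 60.

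**Conclusion.** The mismatch between sections 3.7 and 3.8 is real and should be corrected. Deaths in hospital after day 60 are not captured, and stays beyond 60 days are truncated or missing, mostly among the earliest births. About 22-34% of births would be early enough to be affected on the central assumption, and 14-45% over the range examined. This rests on an assumed discharge age and entry mix and on the protocol's one-week half-life.

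The consequences are confined to the separate comparison of death before discharge and to length of stay, chiefly if it is summarised by a mean. The number of deaths lost cannot be estimated from the protocol. The early-onset sepsis and leukomalacia components have windows of 72 and 96 hours and are untouched, as are the primary outcome, latency and the sample size.

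**What to change.** Add one end-of-stay entry to the CRF for infants in hospital beyond day 60, giving the date and whether the infant was discharged alive or died. Use it for the death component and for length of stay. The cost is a short extra form for a minority of infants and a slightly later database lock. No sample size or power figure changes.

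If that is not feasible, rename the component in section 3.7 as death by discharge or day 60, whichever is first. Treat length of stay as right-censored at 60 days, and state how deaths before discharge are handled. This needs no new data.

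In either case, state in section 3.11 b when the CRF copy is due for an infant still in hospital at day 60. Section 3.10 b triggers the interim analysis on receipt of half the CRFs, so sites should work to one clock.

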### **3.9 Data Analysis**

Primary Outcome. The primary outcome measure is the proportion of women who continue the pregnancy to a favorable gestational age (34w0d or documented fetal lung maturity at 32w0d to 33w6d). The null and alternative hypotheses are as follows:

$$H_0: p_1 = p_2 \text{ and } H_1: p_1 \neq p_2$$

where  $p_1$ =the proportion of women who continue the pregnancy to a favorable gestational age in the progesterone group and  $p_2$ =the proportion of women who continue the pregnancy to a favorable gestational age in the placebo group

To test the null hypothesis, a Cochran-Mantel-Haenszel test will be used, stratified by gestational age group at randomization. The final alpha level will be based on the O'Brien-Fleming spending function and depends on the number and timing of interim analyses. If, as planned, only one interim analysis occurs at 50% of participants randomized, the final alpha level will be

0.049. The primary outcome measure will be analyzed in the intent-to-treat population (i.e. all randomized participants).

Secondary Outcomes. The duration of latency will be determined as the time from randomization until delivery. A staggered entry Kaplan-Meier analysis (which adjusts for gestational age at randomization) will be completed with participants with missing outcome data censored on the date last known pregnant. Significant differences between the progesterone and placebo group will be determined using the log-rank test.

The percentage of participants with at least one of the neonatal morbidity measures (composite neonatal morbidity) will be tested for significant differences between the treatment groups using a Cochran-Mantel-Haenszel test stratified by gestational group at randomization. The percentage of participants with each of the component morbidities (e.g. RDS, NEC, IVH, etc.) will be similarly compared.

All secondary outcome measures will be tested for statistical significance using an alpha level of 0.05. Latency and composite neonatal morbidity will be analyzed in the intent-to-treat population. With the exception of stillbirth (analyzed in the intent-to-treat population), the component morbidities will be analyzed in all participants with a live birth.

Sample Size & Power Calculations. A total of 222 pregnant women (111 in each treatment group) will be randomized in the study. A total sample size of 105 participants is sufficient to detect an absolute increase in the proportion of women reaching a favorable gestational age of

20% (from 30% in the placebo group to 50% in the progesterone group). This sample size was calculated assuming a type I error (2-sided) of 5% and a power of 80% and adjusting for one interim look at 50% of participants randomized. Because PROM patients are hospitalized until delivery, loss-to-follow-up should be minimal, comprising only patients whose membranes reseal & who deliver elsewhere. The planned sample size was increased from 105 patients per group to 111 patients per group to compensate for a loss-to-follow-up rate of 5% or less.

The proposed sample size is also sufficient to detect a 4-day between-group difference in latency, assuming a standard deviation of 10 days with a power of approximately 80%.

The proposed sample size is also sufficient to detect a reduction in neonatal morbidity from 60% in the placebo group to 40% in the 17P group with a power of approximately 80%.

Interim Analysis. One interim analysis of efficacy will be conducted when 50% of participants have outcome data available (111 participants total). The group sequential method of Lan and DeMets will be used to characterize the rate at which the type I error is spent where the spending function is the O'Brien-Fleming boundary. The nominal alpha level at the interim analysis (50% of participants) is 0.0031 and at the final analysis (100% of participants) is 0.049. In addition, a futility analysis will be conducted whereby the probability of finding a significant result at the end of the study will be calculated based on the current trend in the data, the null and alternative hypotheses.

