warranted (Caughey, 2008). In addition, because RDS accounts most of the mortality & major morbidity of premature birth, many clinicians will attempt to assess fetal lung maturity via amniotic fluid analysis at 32-34 weeks of gestation in patients with PROM and will recommend delivery if lung maturity is documented (Caughey, 2008).

Despite an attempt at expectant management, the majority of patients with PROM will be delivered within the first week or so (Bengtson et al., 1989; Dale et al., 1989). The common reasons for this include the onset of spontaneous preterm labor, development of intraamniotic infection, placental abruption, and umbilical cord accident (Combs et al., 2004). The “latency period” (the time from PROM until delivery) roughly follows a “half-life function” with a half-life of about one week (Amon et al., 1988; McGregor et al., 1991; Grable et al., 1996; Mercer et al., 1997). That is, about half the patients with PROM will remain undelivered for the first week, half of those remaining will remain undelivered for another week, half of those for yet another week, etc.

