### **3.5 Group Assignment, Study Medications**

Each patient will be randomly assigned to one of two treatment arms, 17P or placebo.

a. Progesterone (17P) group. Patients in the 17P group will be given 17P, 250 mg IM weekly in 1 ml of oil vehicle.

b. Placebo group. Patients in the placebo group will be given a weekly IM injection of 1 ml of oil vehicle.

Patients, investigators, and study personnel will be blinded as to group assignment. A computer randomization program will be used to generate a randomization code book which will be kept at the pharmacy at each study site hospital. The pharmacy will use the code-book to determine which medication to dispense (17P or placebo) to the patient. The code will not be broken or revealed until all patients have completed the study & their data submitted, unless the data safety/monitoring committee concludes that breaking the code is necessary to evaluate an adverse event.

To ensure balanced group assignments at each study site, randomization will be stratified in 3-week gestational age strata (23w0d-25w6d, 26w0d-28w6d, 29w0d-31w6d).

The assigned medication will be administered by a registered nurse. The administration will be recorded in the inpatient medical record, for example, “Study medication, progesterone or placebo, 1 ml, IM injection in right ventral gluteus” or similar notation as required per hospital policy at each site. The research personnel will also document the medication administration on the participant’s case report form..

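### The primary test is valid, but adjusting for gestational age only in 3-week strata gives up a little power that gestational age in days would recover

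*Protocol*

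**What the plan says.** Section 3.9 fixes the primary test: "a Cochran-Mantel-Haenszel test will be used, stratified by gestational age group at randomization". The only gestational-age groups in the protocol are in section 3.5, where "randomization will be stratified in 3-week gestational age strata (23w0d-25w6d, 26w0d-28w6d, 29w0d-31w6d"). The primary outcome therefore gets a three-level adjustment and no finer one.

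Three other statements matter here:
- Entry covers nine weeks: "Gestational age is between 23w0d and 31w6d, inclusive, at time of enrollment" (section 3.2). Section 3.3 expresses gestational age in weeks and days.
- Success is a fixed target: "34w0d or documented fetal lung maturity at 32w0d to 33w6d" (section 3.9).
- Latency is described in section 2.2 as roughly a half-life function "with a half-life of about one week".

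For the secondary latency outcome, section 3.9 plans a staggered-entry Kaplan-Meier analysis, described as adjusting for gestational age at randomization.

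**The concern.** A woman randomized at 29w0d must stay undelivered for three weeks to reach 32w0d. A woman randomized at 31w6d needs one day. Both fall in the last stratum, and the 3-stratum test treats them as exchangeable. Variation in outcome that is explained by days of gestation within a stratum is left in as noise, although the days are already recorded for every participant.

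What is at stake is a modest amount of power in a trial sized for 80%. The validity of the primary result is not in question.

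**Working it through.** **1. The plan's sample size.** Section 3.9 gives an increase of "20% (from 30% in the placebo group to 50% in the progesterone group"), two-sided 5% error, 80% power and one interim look. The usual two-proportion formula is

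n = [1.960·√(2·0.4·0.6) + 0.842·√(0.3·0.7 + 0.5·0.5)]² / 0.2² = 93 per group.

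With continuity correction it gives 103 (104 at alpha 0.049), close to the stated 105. Then 105/0.95 = 110.5, which rounds up to 111. The plan's figure is reproduced. It makes no use of gestational age.

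**2. A model for success.** Let g be gestational age at entry in days, h the half-life in days and m the share of women reaching 32w0d (day 224) who have lung maturity documented there. Then

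P(success) = 0.5^((224−g)/h) × [m + (1−m)·0.5^(14/h)].

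The half-life of about 7 days comes from section 2.2. It is counted there from membrane rupture and is used here from randomization. The value of m and the distribution of g are assumptions. The runs used m = 1 or 0.5. Entry was either uniform over the 63 days or late-skewed, with weights rising e²-fold so that the strata hold 15%, 29% and 57%.

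**3. Spread within the last stratum.** The ratio of success at 31w6d to success at 29w0d is 2^(20/h), whatever m is.
- h = 7: 2^(20/7) = 7.25. For reaching 32w0d this is 12.5% against 90.6%; for reaching 34w0d it is 3.1% against 22.6%.
- h lengthened until placebo success is 30%: h runs from about 8 to 24 days over both entry mixes and m from 1 to 0, and the ratio from 5.6 down to 1.8.

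The last stratum supplies 88% (uniform) or 94% (late-skewed) of placebo successes at h = 7. When placebo success is set to 30%, the share is about 54% to 93%.

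**4. Power.** Each scenario used 4,000 simulated trials with 210 evaluable women (105 per group), near-balanced allocation within strata and alpha 0.049. Both tests were applied to the same data. The adjusted test is a logistic score test with the strata plus gestational age in days.

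| Entry, m | Half-life, placebo → 17P (days) | Success rates | 3-stratum test | Adjusted | Gain (points) |
|---|---|---|---|---|---|
| Uniform, 1 | set to give rates | 30% vs 50% | 92.2% | 93.3% | 1.2 |
| Uniform, 0.5 | set to give rates | 30% vs 50% | 89.5% | 90.3% | 0.8 |
| Late-skewed, 1 | set to give rates | 30% vs 50% | 92.2% | 95.1% | 2.8 |
| Late-skewed, 0.5 | set to give rates | 30% vs 50% | 89.3% | 91.2% | 1.9 |
| Uniform, 1 | 7 → 13.5 | 15% vs 29% | 78.8% | 83.4% | 4.6 |
| Uniform, 0.5 | 7 → 13.5 | 10% vs 22% | 74.0% | 77.2% | 3.2 |
| Late-skewed, 1 | 7 → 13.5 | 27% vs 43% | 80.0% | 85.5% | 5.5 |
| Late-skewed, 0.5 | 7 → 13.5 | 17% vs 32% | 79.4% | 82.1% | 2.6 |

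The simulation standard error of one power near 90% is √(0.9·0.1/4000) = 0.5 points; the differences are paired. The gain was positive in every alternative scenario. It came close to 7 points only where a smaller effect left the 3-stratum test at about 60% power. Stratifying the same test by completed week gave about −1 to +5 points, so it does not reliably help.

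**5. Type I error.** At the final look, null rejection by the adjusted test was between 0.047 and 0.057 in the runs made, against a nominal 0.049.

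The interim look is different. With 111 women, nominal level 0.0031 and 15,000 null trials per scenario (standard error about 0.0005), the 3-stratum test was compared with a logistic likelihood-ratio test, linear plus quadratic in days. The second entry mix puts 20%, 30% and 50% in the three strata.

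| Entry, half-life | 3-stratum test | Logistic |
|---|---|---|
| Uniform, 7 days | 0.0025 | 0.0068 |
| 20/30/50, 7 days | 0.0025 | 0.0056 |
| Uniform, 16 days | 0.0023 | 0.0037 |
| 20/30/50, 9.5 days | 0.0027 | 0.0038 |

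A further run with a 7-day half-life gave 0.006 to 0.008 for the likelihood-ratio test, and the score test also exceeded the level.

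**The case against.** The planned test has a strong defence. It is valid, it matches the randomization strata, it beats an unstratified test, and it reached at least 80% power for 30% versus 50% with 210 evaluable women in every scenario run. Nothing in the protocol contradicts it. All of this stands, so the point can be no more than a suggested improvement.

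The size of the gain can also be challenged. The larger gains come with the 7-day half-life. With uniform entry that half-life caps placebo success at about 15%, half the planned 30%. The protocol gives the half-life only as approximate and counts it from membrane rupture. A strict half-life function has no memory, so it would carry over to randomization, but the protocol does not claim it is strict. Lung maturity is sampled only where possible (section 3.6), so the chance of reaching 32w0d is not itself the success rate. These objections hold, and they are why the gain near the design alternative is put at 1 to 3 points.

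The most serious objection is to a simple remedy. Moving to an asymptotic logistic test at both looks would, with few successes at the interim, roughly double the chance of a false early efficacy stop in the 7-day scenarios. That stands too, and it shapes the fix.

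A reader might infer that chance imbalance in days within a stratum biases the comparison. It does not: under randomization such imbalance averages to zero, and the test's variance already covers it. Adjustment improves precision; it removes no bias.

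**Conclusion.** The point holds as a minor matter of efficiency. Gestational age in days predicts the primary outcome strongly within a 3-week stratum: about 7-fold with a 7-day half-life from randomization, and about 2- to 6-fold if the half-life is lengthened to give 30% placebo success. Adjusting for it adds about 1 to 3 points of power near 30% versus 50%, and up to about 5 points in other scenarios where power is near 80%.

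The direction was the same in every alternative scenario. The size rests on assumed entry mixes and lung-maturity shares that the protocol does not state.

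A reader might go further and infer that the primary test is wrong, that the trial is underpowered because of it, or that the extra power costs nothing. The documents do not support the first two. The third fails because the error level needs protecting, above all at the interim.

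**What to change.** Amend section 3.9 before unblinding, and preferably before the interim look:

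- **Final primary test:** adjust for gestational age at randomization in days (linear, with or without a quadratic term) in addition to the strata. Take the p-value from permutation within the randomization strata as actually used, including site if the lists are site-specific. Alternatively, keep the asymptotic p-value and document by simulation that type I error is held.
- **Interim look at 0.0031:** keep the 3-stratum Cochran-Mantel-Haenszel test, or use the permutation p-value. Using different tests at the two looks changes their correlation, but total error cannot exceed 0.0031 + 0.049 = 0.0521 if each look holds its level.
- **Supportive analysis:** report the 3-stratum test at the end of the trial.
- **Effect measure:** give a standardised risk difference from the adjusted model.
- **Not recommended:** stratification by completed week, which can lose power.

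The cost is a short amendment, some extra programming, and a risk difference that must be derived from the model because the logistic coefficient is a conditional odds ratio. No further patients or data are needed.

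### The power statement gives 105 as the total sample size for 80% power, but 105 is the per-group figure; the planned 222 women are adequate.

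*Protocol*

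**What the plan says.** All the relevant text is in section 3.9 (Data Analysis) of the protocol.

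- **Planned enrolment:** "A total of 222 pregnant women (111 in each treatment group) will be randomized in the study".
- **Power statement, in the next sentence:** "A total sample size of 105 participants is sufficient to detect an absolute increase" of "20% (from 30% in the placebo group to 50% in the progesterone group").
- **Assumptions:** "assuming a type I error (2-sided) of 5% and a power of 80% and adjusting for one interim look at 50% of participants randomized".
- **Allowance for losses, at the end of the paragraph:** "The planned sample size was increased from 105 patients per group to 111 patients per group", and this is done "to compensate for a loss-to-follow-up rate of 5% or less".
- **Interim design:** "The nominal alpha level at the interim analysis (50% of participants) is 0.0031 and at the final analysis (100% of participants) is 0.049".
- **Primary test:** "a Cochran-Mantel-Haenszel test will be used, stratified by gestational age group at randomization". The method behind the sample-size calculation is not named.

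**The concern.** The number 105 cannot be both the total and the size of one group. The word for total is not ambiguous here, because the sentence just before it uses the same word for both groups combined (222, made up of 111 and 111).

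This sentence is the protocol's justification for its primary-outcome sample size. Read literally, it says that 80% power needs 105 women, which is fewer than half of the 222 to be randomized. Anyone who checks the calculation from that sentence alone will fail to reproduce it, and anyone who copies it into a report will carry a wrong figure forward.

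**Working it through.** **Inputs, all from section 3.9.** Rates 0.30 and 0.50, so d = 0.20 and the mean rate is 0.40. Equal groups, two-sided 5% alpha, 80% power (z = 0.8416). One interim look at 50%, with nominal alphas 0.0031 and 0.049. Loss to follow-up 5%. Stratification is ignored because the protocol gives no stratum-specific rates.

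**1. Interim adjustment.** A two-look Lan-DeMets boundary of O'Brien-Fleming type, solved numerically, gives nominal two-sided alphas of 0.00305 and 0.0490. The protocol's 0.0031 and 0.049 reproduce. The final critical value is z = 1.9686, and the sample-size inflation is only 1.0037. The interim look therefore cannot explain a factor of two.

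**2. Required size per group.** The pooled-variance formula is

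n = [z(α/2)·√(2 × 0.40 × 0.60) + z(β)·√(0.30 × 0.70 + 0.50 × 0.50)]² / d²

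with √0.48 = 0.6928 and √0.46 = 0.6782.

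- Alpha 0.05: (1.9600 × 0.6928 + 0.8416 × 0.6782)² / 0.04 = 93.0.
- Alpha 0.049: (1.9686 × 0.6928 + 0.8416 × 0.6782)² / 0.04 = 93.6, so 94.

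The continuity-corrected size is n′ = (n/4)·[1 + √(1 + 4/(n·d))]².

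- Alpha 0.05: 102.8, so 103.
- Alpha 0.049: 103.3, so 104.

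The stated 105 is within two patients of the corrected per-group figures. As a total it is out of reach by every method tried. The two-sided total runs from about 181 (unpooled variance, 2 × 90.3) to 208 (2 × 104). Even a one-sided test needs 148 (2 × 74) to 166 (2 × 83).

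**3. Power under each reading, alpha 0.049.** Power = Φ{[d·√n − 1.9686 × 0.6928] / 0.6782}, with d replaced by d − 1/n for the continuity correction.

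| Size | Uncorrected | Continuity-corrected |
|---|---|---|
| 105 in total (52.5 per group) | 55.0% | 46.9% |
| 105 per group (210 in total) | 84.4% | 80.7% |
| 111 per group (222 in total, no losses) | 86.3% | 83.0% |

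Worked case, 52.5 per group, uncorrected: (0.20 × 7.2457 − 1.3639) / 0.6782 = 0.126, and Φ(0.126) = 0.550.

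Other methods agree. Fisher's exact test gives 51.8% at 52 and 53 per group and 81.1% at 105 per group. Unpooled variance gives 56.7% at 52.5 per group. The full two-look calculation gives 55.1% (pooled) to 56.8% (unpooled) at 52.5 per group.

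**4. Link to the planned enrolment.** 105 / (1 − 0.05) = 110.5, rounded up to 111 per group, and 2 × 111 = 222. Both planned figures follow from 105 per group. Neither follows from 105 in total.

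**The case against.** The strongest reply is that this is a slip in one phrase which the same paragraph corrects. The sentence before it gives 222 and 111 per group, the closing sentence gives 105 per group, and the interim count of 111 in total is half of 222. Every operational number already rests on the per-group reading. All of that stands, and it is why the point is minor. It does not make the sentence right, since the stated figure is wrong by a factor of two in the place where the sample size is justified.

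A reader might infer two stronger things, and the protocol supports neither.

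- **That the trial is underpowered.** The 47% to 55% belongs to a 105-woman trial that nobody plans to run. The planned 222 gives about 83% to 86% before losses.
- **That the monitoring board could take the interim look, at 111 women, as already fully powered and stop wrongly.** The stopping grounds in section 3.10 are a primary-outcome difference at alpha 0.0031, a conditional-probability judgement and a safety concern. None uses 105. Section 3.9 defines futility by the chance of a significant result at the end of the study, and it labels 111 as 50% of participants.

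Nor can the calculation method be inferred. A continuity-corrected formula and Fisher's exact test both give about 81% at 105 per group, and the protocol does not say which, if either, was used.

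**Conclusion.** The power sentence is wrong as written. The figure of 105 is the evaluable number per group, 210 in total. Under the protocol's own assumptions, 105 per group gives about 81% to 84% power at alpha 0.049 (with and without continuity correction). The same number as a total gives about 47% to 55%, and no method tried takes it above 57%.

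The conclusion rests on equal allocation, rates of 30% and 50%, and an unstratified calculation. The gap between the two readings is far larger than any difference between methods. This is a minor correction of a stated figure, with no consequence for enrolment, alpha, the interim boundary or the analysis.

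**What to change.** In section 3.9, Sample Size & Power Calculations, change the opening of the power sentence to: *A sample size of 105 evaluable participants per group (210 in total) is sufficient to detect …*, and leave the rest of the sentence as it is. The closing sentence, which raises 105 to 111 per group, is already consistent with this. The cost is one sentence of protocol text.
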